#### Data management

Data entered directly into paper case report forms is considered as source data, additional source documentation includes participant study diaries, online questionnaires and focus group/interview audio recordings and transcripts. Data from case report forms and participant diaries will be entered manually into the database allowing for data monitoring and cleansing. Questionnaire data will be received and directly accessible online by only research team members who have the appropriate access. Case report forms will be shared with the coordinating centre via password secured email and a copy retained securely at site. A unique code will be produced for each participant and used on all corresponding documentation and files, to ensure anonymity.

#### Confidentiality

Only anonymised data will be shared with the coordinating centre for analysis. Electronic files with personal information will be password protected and stored on the university partner networks in folders that can only be accessed by the research team. Access to the data collected during the project (including any participant personal data) will be restricted to the research team, and data will not be shared with anyone else. Personal information that may enable the service user to be identified will be removed from interview and focus group transcripts.

Any personal data will be destroyed on completion of the project. The coded data will be stored for five years following the completion of the study, when it will be destroyed.

## Statistical methods

### Statistical methods for primary and secondary outcomes

#### Quantitative data analysis

Descriptive statistics will be used to assess primary and secondary process outcomes such as recruitment rates, adherence rates and completeness of data. Exercise adherence will be compared with outcomes to inform compliance criteria in the full study. In a definitive study, the primary outcome — change from baseline in systolic BP — will be analysed using analysis of covariance (ANCOVA), with a fixed treatment effect allowing adjustments for baseline values, centre, sex and age. This model will be used to estimate differences between the arms and confidence intervals from the feasibility study. Eighty percent and 95% confidence intervals will be calculated. Data from the IE experience questionnaires will be transferred to Stata/IC version 16 and analysed using descriptive statistics.

#### Qualitative data analysis

Thematic analysis of focus group/interview transcripts will be carried out using Braun and Clarke’s [68] six stage model using NVivo version 11 qualitative data analysis software (QSR International Pty Ltd. [2015] NVivo, https://www.qsrinternational.com/nvivo-qualitative-data-analysis-software/home). Drawing on Sweeney et al.’s [69] notion that the service user researcher unique perspective should be preserved rather than subsumed, the process will involve multiple members (including public co-applicants) of the project team. Inductive thematic analysis of focus group/interview transcripts will be carried out using NVivo version 11 (QSR International Pty Ltd. [2015] NVivo, https://www.qsrinternational.com/nvivo-qualitative-data-analysis-software/home). The process will involve reading and re-reading the transcripts and noting down initial ideas. Then the transcripts will be coded. Data extracts will be collated within each code and then codes ordered into potential themes. Subsequently, these themes will then be reviewed and refined. Ongoing analysis will refine the specifics of each theme and identify any themes which have not previously been recognised. Deviant case analysis will be used to ensure that perspectives that diverged from dominant trends are not overlooked.

### Methods in analysis to handle protocol non-adherence and any statistical methods to handle missing data

Missing values will be estimated using a combination of last observation carry forward and baseline observation carried forward (where only baseline data are available) in the secondary analysis of intention to treat.

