### Relevant concomitant care permitted or prohibited during the trial

Exclusion criteria states the participants should not be taking anti-hypertensive medications whilst taking part in the trial.

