### Sample size

Review of current literature revealed few IE studies in a hypertensive population. These studies were small (*n* < 25), conducted under different conditions to the proposed study, and showed low precision and large variability in estimates of the standard deviation (SD). A sample size of 100 participants, 50 per arm, will be used in the study. Allowing for 20% attrition and 6.5% incomplete data, 74 participants (37 in each arm) will have completed change measures at 4 weeks. This is in line with the recommended sample size of 70 to estimate key parameters from external pilot RCTs [62]. A sample size of 74 produces a two-sided 95% confidence interval with a width of 1.33 when the standard deviation is 4. This estimate of 4 has been taken from a previous study (*N* = 24) [10]. The sample size confidence interval has been calculated using Pass11 software (PASS 11. NCSS, LLC. Kaysville, UT, USA, www.ncss.com).

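### The only described analysis of all randomised participants is secondary and fills missing blood pressure by LOCF/BOCF, while the set behind the lead treatment difference is not named

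*Protocol article*

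**What the plan says.** The section of the protocol article on non-adherence and missing data consists of one sentence: "Missing values will be estimated using a combination of last observation carry forward and baseline observation carried forward (where only baseline data are available"), and this is done "in the secondary analysis of intention to treat". No other rule for missing blood pressure is given.

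The primary outcomes include the variance of blood pressure change at week 4 and months 3 and 6. They also include the between-arm difference in systolic change with 80% and 95% confidence intervals, which is to help decide whether a confirmatory trial goes ahead (Outcomes, Primary). The quantitative analysis section names an ANCOVA adjusted for baseline, centre, sex and age, but no analysis set.

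On numbers, the Sample size section says: "A sample size of 100 participants, 50 per arm, will be used in the study". It continues: "Allowing for 20% attrition and 6.5% incomplete data, 74 participants (37 in each arm) will have completed change measures at 4 weeks". The stated precision is: "A sample size of 74 produces a two-sided 95% confidence interval with a width of 1.33 when the standard deviation is 4".

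**The concern.** Two features of the plan combine.

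- **ITT is secondary.** The treatment difference is a primary outcome with a part in the go/no-go decision. If intention to treat is the secondary analysis, the lead estimate presumably uses some other set, and the reader cannot tell which. If participants drop out for reasons related to their blood pressure, a comparison limited to those with complete data loses the protection of randomisation.
- **The ITT analysis uses single imputation.** Baseline carried forward gives a change of exactly zero. Last observation carried forward fixes an earlier reading as if it had been measured later. Both then count as observed data. The analysis that should guard against selective dropout is itself distorted, so neither analysis gives a sound as-randomised estimate.

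A further question is whether the imputed values also reach the variance estimate that is to size the definitive trial.

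**Working it through.** **Step 1. The plan's own figure.** Inputs from Sample size: n = 74, SD = 4, two-sided 95%. The chi-square interval for an SD is SD × √((n−1)/χ²) with 73 degrees of freedom. It gives 3.443 to 4.773, a width of 1.330, which matches the stated 1.33. A t-interval for a mean would be 1.85 wide, so 1.33 is the width for the SD, and it is computed on 74 observed changes.

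**Step 2. Share missing at week 4.** 100 × 0.80 × 0.935 = 74.8, and 100 × (1 − 0.265) = 73.5. Both agree with 74 of 100. The share missing is p = 26/100 = 0.26, or 13 of 50 per arm.

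**Step 3. Assumptions for the imputed set.**
- Missingness is equal in both arms and unrelated to outcome.
- Every missing week-4 change is set to zero. Week 4 is the first follow-up assessment shared by both arms. Table 1 also lists home readings at the exercise arm's early telephone call; these are assumed not to be carried forward.
- Observed changes have SD 4 in each arm, with no mean change in control.
- The exercise-arm mean change μ runs from 0 to −12 mmHg. The 12 is the figure the Introduction gives for pre-hypertensives, so it is an upper scenario and comes from a different population.

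**Step 4. Treatment difference.** The mean after BOCF is (1 − p)μ. At μ = −12 this is 0.74 × (−12) = −8.88 mmHg. Any difference is multiplied by 0.74.

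**Step 5. Variance if it were taken from the imputed set.** Within-arm variance = (1 − p) × 16 + p(1 − p)μ², which is 11.84 + 0.1924μ².

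| Exercise μ (mmHg) | Exercise-arm SD | Pooled SD | Pooled variance ÷ 16 |
|---|---|---|---|
| 0 | 3.44 | 3.44 | 0.74 |
| −4 | 3.86 | 3.66 | 0.84 |
| −8 | 4.91 | 4.24 | 1.12 |
| −12 | 6.29 | 5.07 | 1.61 |

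The definitive-trial sample size scales with the last column. The bias changes sign at an exercise-arm change of about 4 × √(2/0.74) = 6.6 mmHg. If only the 20% attrition is imputed, the variance factor runs from 0.80 to 1.52 and a 12 mmHg difference becomes 9.6.

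**Step 6. Standard error of the difference, unadjusted.**
- Observed cases: √(16/37 + 16/37) = 0.930.
- BOCF, μ = 0: √(2 × 11.84/50) = 0.688, which is 0.74 of the observed-case value.
- BOCF, μ = −12: the exercise-arm variance is 11.84 + 27.71 = 39.55, so √((39.55 + 11.84)/50) = 1.014, which is 1.09 times the observed-case value.

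The error in the standard error therefore changes direction with the size of the effect.

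**The case against.** The strongest reply is that the rule is confined to a secondary analysis. The precision statement uses 74 participants with completed changes, so the 4-week variance is evidently meant to come from observed data. A reader might infer that LOCF/BOCF corrupts the variance the study exists to estimate. The documents do not support that: no sentence says the SD will be taken from imputed data, and the two secondary-analysis words cited above point the other way. This part of the objection stands. It does not fully cover months 3 and 6, because the 74 refers to week 4 only and the outcome list names no set for the later times.

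It can also be said that a completer lead set is nowhere stated, and that the wording would also fit an analysis by randomised arm of whatever was observed. That is fair. The completer reading is an inference from the Sample size and missing-data sections, and defining analysis sets is often left to a fuller document. What the article does fix is that ITT is secondary and that it uses single imputation.

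Two other inferences should be resisted. One is that confidence intervals under BOCF are always too narrow; Step 6 shows a wider one at 12 mmHg. The other is that participants who start blood pressure medication are withdrawn and have an earlier reading carried forward. The concomitant-care section says only that "participants should not be taking anti-hypertensive medications whilst taking part in the trial". No passage says that such participants leave or that their measurements stop, and Table 1 records concomitant medication at each follow-up.

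Finally, BOCF may be defended as conservative. With equal missingness it does pull the difference toward zero. But this study is meant to estimate, and the protocol's Discussion counts unchanged blood pressure as supporting viability, so imputing no change is not clearly conservative here.

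**Conclusion.** The concern holds in a limited form. The only analysis described for all randomised participants is secondary and uses a method that, at the planned missingness, multiplies any treatment difference by about 0.74 (range 0.74 to 0.80 for 26% to 20% imputed). Its standard error is not valid for the true difference: 0.74 to 1.09 times the observed-case value for exercise-arm changes of 0 to −12 mmHg. The lead treatment difference appears to rest on something other than all randomised participants, but the set is unnamed.

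The effect on the variance objective is conditional. If the SD comes from observed changes, the stated precision is unaffected. If it were taken from the imputed set, the pooled variance, and with it the definitive-trial sample size, would be multiplied by about 0.74 to 1.61.

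All of these sizes rest on the Step 3 assumptions. Unequal or outcome-related missingness would change them, and the documents give no missingness figure for months 3 and 6.

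**What to change.** 1. Make the as-randomised comparison the lead analysis: a linear mixed model on all observed systolic pressures at week 4 and months 3 and 6, with arm by time and the covariates already named (baseline, centre, sex, age).
2. Drop LOCF and BOCF and use multiple imputation instead. Participants with only a baseline value add nothing to a model of post-baseline readings, so imputation is what brings them into the comparison. Add a delta-adjusted version as sensitivity analysis.
3. State that the SD for the definitive trial comes from observed changes at each time point, with its confidence interval based on the number actually observed.

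The cost is slightly more analysis work and reliance on a missing-at-random assumption, which the delta-adjusted analysis tests. The change needs no extra participants or visits.

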### Plans to give access to the full protocol, participant level-data and statistical code

Anonymised data will be made available to researchers at universities, NHS organisations or other healthcare providers where the sharing of data has a clear defined purpose and its use will be of benefit to wider society.

## Oversight and monitoring

### Composition of the coordinating centre and trial steering committee

Delivery of the project is a collaboration between the Section of Sport, Exercise & Rehabilitation Sciences, Canterbury Christ Church University (CCCU), the Centre for Health Services Studies, University of Kent (UKC) and East Kent Hospitals University Foundation Trust (EKHUFT).

Two groups were established to provide appropriate oversight of the study and ensure this is maintained from various perspectives, the Study Steering Committee (SSC) and the Project Management Group (PMG).

The SSC is comprised of at least 75% independent members and includes the project co-leads, an independent statistician, a health economist, a clinician with expertise in hypertension/clinical trials/primary care, an exercise specialist and two independent lay members. The SSC meets tri-monthly to critically oversee progress, outputs, deliverables and governance of the project; have oversight of delivery of the study on behalf of the funder to ensure achievement of study objectives within agreed timelines; ensure the protection of rights and safety of study participants; regularly review of ongoing project data; and periodically review of safety data to ensure patient safety throughout [70]. In doing so, the SSC reports directly to the funder. The SSC will consider the need for any interim analysis based on reports received and may consider data emerging from other related studies and make recommendations for this study based on these. The SSC will also consider whether further time or funding is required for any aspect of the study and advise where best this may be obtained.

The PMG is comprised of 2 co-chief investigators, 4 co-applicants (including the project manager), 1 statistician, 1 health economist, 2 public co-applicants, 1 research facilitator and 1 study coordinator [70]. The members of PMG were responsible for the elaboration of this protocol and meets fortnightly with the purpose of maintaining clear oversight of study delivery according to the protocol, original grant application and subsequent changes; assessing the progress of the study and identifying any barriers to completion; agreeing mitigation plans and actions for any barriers to study completion, e.g. the current Covid-19 pandemic; providing advice to the Chief Investigators; ensuring the protection of rights and safety of study participants; and reporting on study progress to the SSC and funder.

The organizational study chart will include the sponsor EKHUFT, the SSC, the PMG, the two research units; UKC as lead on Qualitative data (health economics, focus group, interviews, patient participant involvement etc.) and CCCU as lead on quantitative data (intervention delivery, fidelity and patient outcomes etc.), the clinical research lead and the investigators at each primary care recruitment sites in SE England.

### Composition of the data monitoring committee, its role and reporting structure

A data monitoring committee is not needed for this study because the intervention is non-invasive with minimal risk of harm.

### Adverse event reporting and harms

An adverse event (AE) is any untoward medical occurrence in a study participant. A serious adverse event (SAE) is any untoward medical occurrence that: results in death, is life-threatening, requires inpatient hospitalisation or prolongation of existing hospitalisation, results in persistent or significantly disability/incapacity or consists of a congenital anomaly or birth defect. Other ‘important medical events’ may also be considered serious if they jeopardise the participant or require an intervention to prevent one of the above consequences.

Only AEs resulting (definitely or probably) from study procedures or the intervention will be collected by the research team and recorded in the participant’s medical records. These may be volunteered by the participant or discovered by the investigator or healthcare professional conducting study visits/follow-up telephone calls. They should be documented throughout the entirety of the study from randomisation until month 6 of intervention. Each AE will be evaluated by the Principal Investigator (PI) for seriousness, causality and expectedness.

A list of potential isometric exercise specific AEs was provided to the HCPs/investigators.

All SAEs will be recorded within 24 h of knowledge of the event. The SAE will be evaluated by the PI and when necessary, in collaboration with the Chief investigator (CI) (highly experienced renal consultant). The CI will report all SAEs to the Sponsor and the Research Ethics Committee within the conditions of ethical approval. The Study Steering Committee will periodically review safety data to ensure patient safety throughout.

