### Participant timeline

The participant timeline is presented in Table 1.

**Table 1 Tab1:** Participant schedule of events

Assessment	Remote screening assessment day 14	Study time point					
		Baseline assessment day 1 (remotely)	IIET visit (within 7 days of Baseline visit)	Follow up telephone call — IE arm only (within 7 days of IIET visit)	Assessment 2 day 28–33 (remotely)	Assessment 3 month 3 (± 7 days) (remotely)	Assessment 4 month 6 (± 7 days) (remotely)
Medical history	X	X					
Concomitant medication	X	X		X	X	X	X
Consent	X						
Observed blood pressure and heart rate		X			X	X	X
IE ability test	X						
Incremental IE test and IE programme provided (for those randomised to intervention arm only)			X				
AE review				X	X	X	X
Diet questionnaire		X			X	X	X
Exercise questionnaire		X			X	X	X
Quality of life questionnaire		X			X	X	X
Collection of IE exercise diary (for those randomised to intervention arm only)				X	X	X	X
Collection of home blood pressure and heart rate readings	X (between day 7 and day 1)	X		X	X	X	X
Health resource use questionnaire					X	X	X
IE experience questionnaire					X		

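### Non-serious adverse events are recorded only if definitely or probably related and only from randomisation, so possibly related events and harms of the screening exercise test are lost and counts by arm are not comparable

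*Protocol article*

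**What the plan says.** The section on adverse event reporting and harms starts from a broad definition: "An adverse event (AE) is any untoward medical occurrence in a study participant". It then narrows what is kept: "Only AEs resulting (definitely or probably) from study procedures or the intervention will be collected by the research team". The time window follows: "They should be documented throughout the entirety of the study from randomisation until month 6 of intervention". After that comes the assessment step: "Each AE will be evaluated by the Principal Investigator (PI) for seriousness, causality and expectedness".

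Serious events are treated differently. The definition begins "A serious adverse event (SAE) is any untoward medical occurrence that: results in death, is life-threatening", and the recording rule is "All SAEs will be recorded within 24 h of knowledge of the event". Neither sentence contains a relatedness condition.

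Table 1 (Participant timeline) marks the "IE ability test" and consent at the remote screening assessment. Adverse event review is marked at the exercise-arm telephone call and at the assessments at day 28–33, month 3 and month 6. It is not marked at screening, baseline or the incremental test visit. The blinding section says that neither participants nor the professionals delivering the exercise are blinded.

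**The concern.** Two features of the collection rule remove information that cannot be recovered later.

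- **Relatedness is a condition for being collected.** An event that someone thinks is only possibly due to the exercise is not written down, so the investigator, the Study Steering Committee and the designers of the later trial cannot revisit that judgement. Because allocation is known, opinion about relatedness can depend on the arm.
- **The clock starts at randomisation.** One exercise procedure, the ability test, is performed before then.

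At stake is the usefulness of the non-serious safety record from a study meant to inform a definitive trial of an intervention that, by the article's own account, has not been tested in an NHS setting. The Study Steering Committee is to review safety data periodically, and there is no data monitoring committee. A low count in the exercise arm would be a count of events attributed to the exercise, not of events that occurred, and the control arm would offer little background rate to set against it.

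**Working it through.** The document gives no adverse event rate, harm endpoint or safety precision, so there is no stated figure to reproduce. The check sets the statements side by side and adds one illustration with assumed values.

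**1. Definition against collection.** The definition has no relatedness condition. The collection rule keeps only the two highest relatedness categories. Events judged possible or unlikely are adverse events by definition but are not collected unless they are serious.

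**2. Order of filter and assessment.** Causality is one of the three things the investigator evaluates for each event, but the events collected are those already regarded as definitely or probably related. Read in sequence, the formal grading can confirm or downgrade a recorded event. It cannot bring back one left out as only possibly related.

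**3. Window against schedule.**

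| Procedure | When | Inside the window? |
|---|---|---|
| Exercise ability test | Remote screening, after consent | No |
| Incremental wall squat test | Visit for those randomised to exercise | Yes |
| Home training | After the incremental test, to month 6 | Yes |

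The ability test must precede randomisation: the section on random allocation randomises only those who meet the criteria, and inability to do the exercise is an exclusion. Harms of study procedures are in scope, yet this procedure lies outside "documented throughout the entirety of the study from randomisation until month 6 of intervention". The intervention description calls failure of the incremental test a screen failure, although Table 1 reserves that test for participants already randomised. The wording should be reconciled, but that test is covered by the window.

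**4. Opportunities to report.** Table 1 gives the exercise arm 1 + 3 = 4 adverse event reviews and the control arm 3.

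**5. What the filter alone can do (illustration).** The 50 per arm is from the protocol; the rates are assumptions.

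- True all-cause non-serious risk of 20% in both arms: 50 × 0.20 = 10 events per arm, a true difference of zero.
- Share called definitely or probably related in the exercise arm, 20% to 60%: 10 × 0.20 = 2 to 10 × 0.60 = 6 recorded.
- Same share in controls, 0% to 10%: 10 × 0 = 0 to 10 × 0.10 = 1 recorded.

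The record would show 2 to 6 against 0 to 1. The apparent excess of 1 (2 − 1) to 6 (6 − 0) events would come wholly from the rule, while 4 to 8 of the 10 exercise-arm events would go unrecorded.

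**6. Serious events.** All are to be recorded, whatever their cause, and three reviews are shared by both arms. A comparison by arm is available, though imprecise with 50 per arm.

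**The case against.** The strongest defence is that collecting related non-serious events plus all serious events is a deliberate and proportionate choice for a 100-participant feasibility study of a non-invasive exercise. Comparative adverse event rates are not among the objectives or outcomes, nor in the Discussion's list of parameters needed for the definitive trial. This stands as a reason for moderate weight. It does not remove the inconsistency between scope and window, or the loss of possibly related events.

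The article also does not say who applies the relatedness condition. It could be read to mean that the investigator's own evaluation decides what the research team collects. On that reading the judgement is better placed, but events graded below probable are still not collected.

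Several stronger readings are tempting, and the document does not support them:

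- **That no comparison of harms between arms is possible.** Serious events are recorded regardless of relatedness, and reviews at 4 weeks, 3 months and 6 months apply to both arms. Only the non-serious comparison is compromised.
- **That control counts are zero by construction.** Controls also undergo study procedures such as home blood pressure measurement, and receive lifestyle advice that includes vigorous exercise. Far fewer of their events are likely to qualify, but not necessarily none.
- **That every harm at screening is lost.** The randomisation start is attached to the non-serious text, and no start is stated for serious events. Loss of serious events before randomisation is not established.
- **That the missed screening harms bias the comparison of arms.** The ability test precedes allocation, so its omission loses information without favouring either arm.

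**Conclusion.** The concern holds for non-serious adverse events. Possibly related events are not collected, non-serious harms of the screening ability test fall outside the recording window despite being in scope, and non-serious counts by arm will reflect the collection rule as well as the treatment. It does not extend to serious events.

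The size of the loss is unknown. The 2 to 6 against 0 to 1 illustration rests on an assumed 20% risk in both arms and assumed attribution shares; it shows direction and is not an estimate. The conclusion about causality grading assumes that the sentences describe the order of operations. The conclusion about unequal counts assumes that fewer control events will be judged related, which is likely with known allocation and no exercise prescription in that arm. The point is worth correcting because data left unrecorded cannot be recovered at analysis, but it does not threaten the primary objectives.

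**What to change.** - Record all adverse events in both arms, or at minimum include possibly related ones, from consent to month 6. Have the investigator grade causality after recording.
- Add an adverse event question at the existing screening and baseline contacts. Table 1 has no review there, and participants who fail screening never reach the later ones.
- Tabulate non-serious events by arm at the shared 4-week, 3-month and 6-month reviews. List events reported at the exercise-only telephone call separately, because controls have no such contact.
- State the start of recording for serious events, and reconcile the screen failure wording for the incremental test with its place after randomisation.

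The cost is some extra form completion and data entry for about 100 participants and for those who fail screening. No new visits are needed. The change concerns recording only and leaves the intervention and participants' care as they are.
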